### Aims and hypotheses

1.1

This study aims to compare suicide risk estimates across different populations and conditions. Specifically, the objectives are: (i) to compare suicide risk evaluations across the different study groups; (ii) to examine the temporal stability of suicide risk estimates when participants evaluate different but comparable clinical scenarios over time; and (iii) to assess whether the use of a structured instrument (C-SSRS) is associated with greater convergence in risk classification compared to unstructured judgment based on personal or clinical impressions. In addition to group-based comparisons, the study will examine whether differences are better explained by dimensional indicators of clinical experience rather than by professional labels alone.

Additionally, based on the expected results, the following hypotheses were formulated:

*HP 1*: Greater clinical experience and prior exposure to suicide-specific training will be associated with higher agreement and more consistent suicide risk estimates, regardless of professional category (Aim 1).

*HP 2*: Differences in risk estimation are expected to reflect variability in clinical exposure to acute suicidal presentations rather than disciplinary background per se (Aim 1).

*HP 3*: All study groups will show lower agreement for intermediate risk categories compared to low and high-risk categories (Aim 1 and 2).

*HP 4*: Greater within-subject variability is expected among individuals with limited or no clinical exposure to suicidal behavior compared to those with greater prior clinical exposure. This expectation is based on the idea that personal experiences, momentary emotional states, and situational cues may exert a stronger influence on individuals who are not familiar with clinical decision-making, whereas healthcare professionals are trained to rely primarily on clinical information and data (Aim 2).

*HP 5*: Participants assigned to the experimental condition (brief training on suicide risk assessment and use of the C-SSRS) will exhibit greater between-subjects and within-subject agreement in suicide risk estimates across all study groups (Aim 3).

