**Figure 2 f2:**
[figure not shown]
Conceptual framework of the CARE study showing the baseline and follow-up assessments.

The questionnaire will be designed so that each participant will be randomly assigned to 6 different vignettes to be evaluated, 2 for each risk category (low, moderate, and high). Specifically, participants assigned to the C-SSRS condition will complete a brief training module on basic suicidology notions embedded within the online questionnaire before evaluating the vignettes. The module is delivered as a single self-administered page and requires approximately 5 minutes to be completed. It is divided into two sections: first, it will provide concise definitions of suicide-related constructs, including thoughts of death, suicidal ideation, suicidal planning, non-suicidal self-injury, suicide attempt, and suicide death, in order to reduce interpretative variability across respondents; second, it will present step-by-step instructions on how to use the C-SSRS (14), explaining the logic of the six screening questions, when conditional questions are administered, and how responses map onto the three risk categories defined by the scale (low, moderate, high). Ultimately, participants will be provided with access to the official Italian version of the C-SSRS and informed that a mobile application version can be used if preferred. No feedback, supervision, or competency assessment will be provided, thereby reflecting the type of brief orientation often available in real-world implementation settings. The remaining participants will be asked to provide a subjective estimation of perceived suicide risk based on their impressions, knowledge, personal judgment, or clinical experience (for clinicians). Notably, for participants without a clinical background, the task is framed as an estimation of perceived suicide risk rather than a diagnostic or clinical evaluation. They will not be required to make clinical decisions but are instead asked to describe how they would interpret and respond to the situation described in the vignette. Participants assigned to the C-SSRS condition will be instructed, for each vignette, to provide a categorical rating of suicide risk as defined by the scale (low, moderate, high); whereas those assigned to the No-C-SSRS condition will be asked, for each vignette, to provide an ordinal risk estimate on a scale from 1 (very low risk) to 9 (imminent risk). Notably, the use of different response formats across conditions reflects the distinct decision-making frameworks under investigation. The C-SSRS operationalizes suicide risk through predefined categorical classifications and does not provide a continuous scoring system, while a 1–9 ordinal scoring metric will be adopted for the No-C-SSRS condition to better capture the natural variability of subjective risk appraisal without imposing a fixed, limited categorization. This approach allows the study to compare two ecologically valid assessment paradigms, structured categorical evaluation versus dimensional judgment, rather than two versions of the same measurement model.

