#### Follow-up assessment

2.3.2

Two weeks after completing the baseline questionnaire, each participant will receive an email reminder to complete the follow-up questionnaire. The follow-up assessment will require participants to evaluate 6 vignettes (2 per risk category), randomly selected from the same pool of 18 vignettes, to examine consistency between baseline and follow-up ratings. Notably, different vignettes are intentionally administered at follow-up to avoid recall effects and to evaluate the temporal stability of participants’ general risk estimation approach rather than agreement on identical cases. Participants assigned to the C-SSRS condition at baseline will again be asked to provide a categorical rating of suicide risk as defined by the C-SSRS (low, moderate, high), although no informational training will be provided at follow-up. Concurrently, participants in the No-C-SSRS condition will be asked, for each vignette, to provide an ordinal suicide risk rating from 1 (very low risk) to 9 (imminent risk), following the same procedure used at baseline. If participants do not complete the follow-up questionnaire within five days of receiving the first reminder, up to three additional reminders will be sent, each one three to five days apart.

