#### Outcomes

2.4.2

The primary outcome will be the assessment of discrepancies in suicide risk estimates across study groups (between-subjects) and the evaluation of the stability of individual risk appraisal tendencies over time (within-subject), in order to identify specific patterns and factors that may influence variability and inter-rater agreement in risk estimation across different clinical scenarios.

The secondary outcome is the assessment of discrepancies in suicide risk estimates between the C-SSRS and No-C-SSRS conditions, in order to determine whether the use of a standardized suicide risk assessment instrument will lead to greater homogeneity in risk ratings across the study groups. To allow comparison of discrepancies between the two subgroups, suicide risk assessment will be expressed as categorical variables for participants assigned to the C-SSRS condition (low, moderate, high) and as ordinal scores for participants in the No-C-SSRS condition (from 1 to 9). Cut points were defined *a priori* to represent three clinically interpretable categories of risk intensity, corresponding to low (scores 1-3), intermediate (4–6), and high (7–9) perceived risk. This mirrors the three-level structure imposed by the C-SSRS while preserving the ordinal distribution of the original ratings (**Table 1**).

**Table 1 T1:** Conversion of the suicide risk estimates between the C-SSRS and No-C-SSRS conditions.

C-SSRS condition risk categories	No-C-SSRS condition risk scores
Low risk	1-2–3 scores
Moderate risk	4-5–6 scores
High risk	7-8–9 scores

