#### Planned statistical analysis

2.5.2

Analyses will examine discrepancies in suicide risk assessment across participant groups and over time to identify factors associated with variability. Descriptive statistics will summarize sociodemographic and professional characteristics of the sample, distribution of risk ratings, and follow-up completion rates. Given the hierarchical structure of the data, with multiple vignette ratings nested within participants, mixed-effects regression models will constitute the primary analytical approach. Random intercepts will be specified for participants to account for repeated ratings within individuals and, when appropriate, for vignettes to account for shared variance attributable to scenario characteristics. Fixed effects will include study group, experimental condition (C-SSRS vs. No-C-SSRS), time (baseline vs. follow-up), and their interactions.

Ratings collected on the 1 to 9 scale will be treated as ordinal variables. Accordingly, ordinal mixed-effects models will be used as the primary approach, whereas linear models treating the scale as continuous will be conducted only as sensitivity analyses to ensure robustness of findings. To evaluate potential bias related to categorization thresholds, sensitivity analyses will include alternative binning strategies (e.g., 1–2 vs. 3–7 vs. 8–9) and models using the full 1–9 scale without categorization.

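### The primary mixed model has no participant-by-time random effect, so its group-by-time and condition-by-time tests reject too often if individuals drift between the two visits

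*Protocol article*

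**What the plan says.** Section 2.5.2 (Planned statistical analysis) makes mixed-effects regression the main method; for the 1 to 9 ratings, "ordinal mixed-effects models will be used as the primary approach" and linear models are sensitivity analyses. The random effects are named. For people: "Random intercepts will be specified for participants to account for repeated ratings within individuals". A second intercept is conditional; it is to be added "when appropriate, for vignettes to account for shared variance attributable to scenario characteristics". The fixed effects in the same model are study group, condition, "time (baseline vs. follow-up), and their interactions". A later paragraph of 2.5.2 sends interaction tests to this framework. No participant-by-time effect or random slope for time is named.

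On the data, section 2.3.1 says "each participant will be randomly assigned to 6 different vignettes to be evaluated, 2 for each risk category", and section 2.3.2 says "The follow-up assessment will require participants to evaluate 6 vignettes (2 per risk category" at two weeks. One intercept therefore covers up to 12 ratings made in two sittings.

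On what is expected, HP 4 in section 1.1 states: "Greater within-subject variability is expected among individuals with limited or no clinical exposure to suicidal behavior". It attributes this partly to mood and circumstances at the time. Section 2.4.2 includes in the primary outcome "the evaluation of the stability of individual risk appraisal tendencies over time (within-subject".

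Section 2.5.2 also plans within-person analyses on one summary per participant per time point: Wilcoxon signed-rank tests and correlations in the No-C-SSRS condition, and consistency indices in the C-SSRS condition.

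**The concern.** With a single participant intercept, two ratings from the same sitting are taken to be no more alike than two ratings made two weeks apart. If a person is more cautious at follow-up than at baseline, all six follow-up ratings carry that shift. The model has nowhere to put it except the residual, so it counts one shift as six nearly independent pieces of evidence.

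The fixed time terms absorb change common to a group. They do not absorb individual departures from it. The mechanism given under HP 4 would produce exactly such departures, because mood and circumstances act on a whole sitting.

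At stake are the time, group-by-time and condition-by-time tests. With random individual drift and no mean change in any group, the model could report that groups change differently over time.

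**Working it through.** **The plan's own figure.** One-way ANOVA, 10 groups, f = 0.20, alpha 0.05, N = 400: noncentrality 400 × 0.20² = 16, df 9 and 390, power 0.800 (0.799 at N = 399). The stated minimum of 400 reproduces. It concerns the baseline comparison only and is not in dispute.

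**Inputs from the protocol article.** Six ratings per sitting, two sittings, ten groups (so group-by-time has 9 df), alpha 0.05.

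**Assumptions.** The documents give no variance components. Let r = participant-by-time variance / residual variance. The residual SD is set at 1.2 (variance 1.44) and the occasion-level SD is varied. Vignette differences are modelled.

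**Formula.** For a participant seen twice, the true variance of the change in mean rating is proportional to 1 + 6r. The intercept-only model pools the drift into a residual with 11 df per person, so it takes that variance as proportional to 1 + 6r/11. Hence

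inflation = (1 + 6r) / (1 + 6r/11).

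Actual error at nominal 5% is P(χ²₉ > 16.92/inflation) for group-by-time and P(|Z| > 1.96/√inflation) for a 1-df term such as time.

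| Occasion SD | r | Inflation | 16.92/inflation | Group-by-time | 1-df time term |
|---|---|---|---|---|---|
| 0 | 0 | 1.00 | 16.92 | 5% | 5% |
| 0.1 | 0.0069 | 1.0417/1.0038 = 1.038 | 16.30 | 6.1% | 5% |
| 0.2 | 0.0278 | 1.1667/1.0152 = 1.149 | 14.72 | 9.9% | 7% |
| 0.3 | 0.0625 | 1.3750/1.0341 = 1.330 | 12.72 | about 17.5% | 9% |
| 0.5 | 0.1736 | 2.0417/1.0947 = 1.865 | 9.07 | 43.1% | 15% |

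For scale: with an assumed participant SD of 0.8, an occasion SD of 0.3 lowers the correlation between a person's two visit means from 0.64/(0.64 + 0.24) = 0.73 to 0.64/(0.64 + 0.09 + 0.24) = 0.66.

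**Simulation check of the formula.** No-C-SSRS arm, 250 participants, 25 per group, 57.5% followed up, no true time or group-by-time effect, vignettes adjusted for:
- Ordinal (cumulative-logit) model, 800 runs per setting: group-by-time rejects 6.6%, 27.1% and 56.8% at r = 0, 0.10 and 0.25. The formula gives 5%, 26.5% and 56.6%.
- Linear model, 400 runs per setting: 4.5%, 25.5% and 57.0%.

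Simulations with the SDs above and ratings confined to 1 to 9 came out somewhat lower than the table. At occasion SD 0.3 and 0.5, group-by-time rejected 10 to 15% and 30 to 34% in the linear model, and 14% and 38% in the ordinal model.

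**Without vignette effects.** With assumed category means of 2.5, 5 and 7.5, the spread between risk categories enters the residual. The linear tests then rejected 0 to 5% (time) and 0 to 9% (group-by-time) over r = 0 to 0.5, so they are conservative over most of the range.

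**With a participant-by-time intercept added (linear model).** Group-by-time rejection was between 2% and 8.5% across the simulations. The 8.5% came from 200 runs, with a simulation error of about 2 points; without the term, the matching figures were 25.5% and 57.0%. The remedy was not simulated in the ordinal model. Condition-by-time and the three-category C-SSRS arm were not simulated either.

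**The case against.** The best defence is that the plan already keeps its within-person outcome away from this problem. The analyses on participant-level summaries use one value per person per visit, so nothing is counted six times. They carry the stability part of the primary outcome, and the Wilcoxon test guards the overall time effect in the No-C-SSRS arm. This stands. A reader might infer that the study cannot address HP 4, or that its within-subject outcome is compromised; the documents do not support that, because the time terms of the mixed model are not the planned measure of instability.

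Second, none of HP 1 to HP 5 predicts that group means change differently over two weeks. This stands too and limits the severity. The interactions are nevertheless in the stated model, and the summaries offer no substitute test for group-by-time or condition-by-time.

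Third, the size rests on assumed variances and on vignette effects being modelled. That is true, and at an occasion SD of 0.1 the excess is only about one point. Eighteen vignettes at three risk levels do call for vignette terms, however, and omitting them would exchange one miscalibration for another.

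Fourth, a condensed article may leave covariance detail to a fuller plan. This has some force, since the text does not say that the named random effects are the only ones. But a structure is stated, and as stated it lacks the occasion level.

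The planned false discovery rate adjustment does not answer the point. It handles multiplicity among valid p-values and cannot correct p-values that are too small.

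**Conclusion.** The point holds in a limited form. As specified, the primary model gives standard errors that are too small for time, group-by-time and condition-by-time if participants drift individually between visits. Group-by-time suffers most: about 6%, 10%, 17% and 43% rejection at a nominal 5% for occasion SDs of 0.1, 0.2, 0.3 and 0.5, with simulations on the bounded scale somewhat lower at the last two. By the same formula a 1-df time term reaches about 15% at SD 0.5.

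These figures assume a residual SD of 1.2 and modelled vignette effects. HP 4 gives a direction but no magnitude, so a reader should not infer that false positives are certain or large. Nor does the model assume that nobody changes: it permits group-wide change and excludes only individual deviation from it. The baseline group comparison behind the sample size is untouched. This should be fixed before analysis, but it does not threaten the study's main inferences.

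**What to change.** In section 2.5.2, specify random intercepts for participants and for participant-by-time (occasion within participant), together with vignette intercepts, in both the ordinal and the linear models. Test time, group-by-time and condition-by-time against that structure. Report the participant-by-time variance as a supplementary measure of instability beside the planned participant-level summaries.

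Letting that variance differ by group should be optional and exploratory. The expected 275 to 300 completers over 10 groups and 2 conditions give only about 14 to 15 per cell (275/20 to 300/20), and such a model was not tested here.

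The cost is a line of text and one variance component, with no new data. Intervals for the time terms will be wider, and the new variance will occasionally be estimated at zero.

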### Study design

2.1

The CARE study will employ a vignette-based randomized experimental design with experimental (C-SSRS) and non-experimental conditions (No-C-SSRS), which will focus on a brief suicidology training and the use of the C-SSRS scale for performing suicide risk estimates. This brief training module is intended to standardize the comprehension of the structured tool rather than to deliver skills-based training. The online survey questionnaire will be conducted through the Qualtrics software platform (https://www.qualtrics.com). Notably, the 18 vignettes that will be used in the present project were provided by the corresponding author of a previous study (20), who granted permission for their use in this project. These vignettes were translated into Italian specifically for the purposes of this study by members of the research team fluent in both languages and familiar with suicidology terminology. The translated version was then reviewed collectively by all authors to ensure semantic accuracy, conceptual equivalence, and clarity of clinical meaning within the Italian sociocultural context. Any discrepancies were resolved through consensus discussion, and the final version was approved by the full author group. No formal pilot testing was conducted before study launch, as the vignettes were originally developed for research purposes and are used here to examine comparative judgment patterns rather than to validate the scenarios themselves.

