To quantify inter-rater agreement across raters for each vignette, Krippendorff’s alpha will be used as the primary agreement index, as it is appropriate for multi-rater settings with potentially unbalanced data. Weighted kappa coefficients will be computed only in supplementary pairwise comparisons to facilitate interpretability relative to commonly reported agreement metrics. Within-person analyses will evaluate the stability of participants’ overall level and pattern of risk estimates across time using different vignette sets drawn from the same risk-calibrated pool. These analyses do not represent test–retest reliability of identical stimuli but rather the temporal consistency of risk perception. Because different vignettes of the same risk category will be administered at baseline and follow-up, within-person analyses will be conducted on participant-level summary indices (e.g., central tendency of ratings and distribution of risk categories across vignettes at each time point) rather than on vignette-level paired comparisons. For the No-C-SSRS condition, paired non-parametric tests, such as the Wilcoxon signed-rank test, and correlation analyses will be used. For the C-SSRS condition, indices of temporal consistency will be computed to evaluate the stability of participants’ overall tendency to classify scenarios into risk categories across time, rather than agreement on identical stimuli.

The mixed-effects framework described above will also be used to examine interaction effects. Pre-specified interaction terms will examine whether differences in risk estimation vary as a function of demographic and professional variables (e.g., age, gender, years of clinical experience, prior suicide-specific training) across study group and experimental condition. In addition, to control for inflation of Type I error due to multiple comparisons, p-values from secondary analyses will be adjusted using the false discovery rate approach.

Missing data will be handled under a missing-at-random assumption using maximum likelihood estimation within mixed-effects models, which allows inclusion of all available observations without listwise deletion. Attrition between baseline and follow-up will be examined descriptively, and sensitivity analyses will compare participants who completed follow-up with those who did not. Predictors of attrition will be explored to assess potential systematic differences between completers and non-completers.

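### Krippendorff's alpha computed for each vignette is uninformative, and the pooled reading still leaves HP3 without an agreement index

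*Protocol article*

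**What the plan says.** Planned statistical analysis (2.5.2) sets purpose and index in one sentence: "To quantify inter-rater agreement across raters for each vignette, Krippendorff’s alpha will be used as the primary agreement index". The reason given is that alpha suits many raters and unbalanced data. Weighted kappa is kept as a supplement for pairwise comparisons. No other index of agreement between raters is named.

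Aims and hypotheses (1.1) contains HP3, which needs agreement separately by risk category: "All study groups will show lower agreement for intermediate risk categories compared to low and high-risk categories".

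On the data, Study design (2.1) refers to "the 18 vignettes that will be used in the present project". Under Baseline assessment (2.3.1), "each participant will be randomly assigned to 6 different vignettes to be evaluated, 2 for each risk category (low, moderate, and high". Ratings are on three levels in the C-SSRS condition and on 1 to 9 in the other condition, the latter also grouped as "corresponding to low (scores 1-3), intermediate (4–6), and high (7–9) perceived risk".

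**The concern.** Alpha compares disagreement within units with the disagreement expected if all ratings were pooled over units. It therefore needs several units that differ. A single vignette offers none, so an alpha for each vignette cannot separate near-unanimity from near-chance rating.

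Inter-rater agreement is part of the primary outcome (Outcomes, 2.4.2), and HP1, HP3 and HP5 are all worded in terms of agreement. If the index is found to be empty only once data are in, its replacement will be chosen after the ratings have been seen.

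**Working it through.** **The plan's own figures.** The article gives no expected value, precision or sample size for alpha. Its one sample-size calculation (ten-group ANOVA, f = 0.20, two-sided 0.05) reproduces: N = 400 gives power 0.8003. It does not bear on this point.

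**Step 1. One vignette (algebra, no assumptions).** Alpha = 1 − Do/De. For one unit with m ratings and category counts n_c:

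- observed coincidences, c ≠ k: n_c·n_k/(m − 1)
- expected coincidences, c ≠ k: n_c·n_k/(n − 1), where n is the number of ratings over all units

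With one unit n = m, so the two are identical, Do = De and alpha = 0 under any distance metric. If all raters agree, alpha is 0/0.

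Example with 83 ratings. This is about what 500 participants give if allocated 1:1 with vignettes drawn evenly: 250 × 6/18 ≈ 83 per vignette per condition at baseline. For counts 82/1/0, the observed low–moderate cell is 82 × 1/82 = 1, and the expected cell is also 1. Numerically, 82/1/0, 78/4/1, 51/22/10 and 33/31/19 all return 0 (to rounding) with nominal, ordinal and interval metrics.

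**Step 2. Vignettes as units of one pooled alpha.** Assume six vignettes per category (18/3; the split is not stated) and these probabilities of a low/moderate/high rating:

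- low vignettes: 0.90/0.09/0.01
- moderate vignettes: 0.20/0.60/0.20
- high vignettes: 0.01/0.09/0.90

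Simulated ordinal alpha over all 18 is 0.71. The expected proportion of rater pairs in the same category is the sum of squared probabilities: 0.81 + 0.0081 + 0.0001 = 0.82 for low and for high, and 0.04 + 0.36 + 0.04 = 0.44 for moderate. The pattern predicted by HP3 is present, but the single pooled figure cannot show it.

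**Step 3. Alpha within a risk category (not in the plan, but the obvious extension).** In the same scenario the vignettes within a category are interchangeable, and alpha is 0.00/0.00/0.00 for low/moderate/high.

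Now let three moderate vignettes be rated 0.70/0.28/0.02 and three 0.02/0.28/0.70. Moderate alpha becomes 0.64, while low and high stay at 0.00. Yet moderate pairwise agreement is 0.49 + 0.0784 + 0.0004 = 0.57, against 0.82. A milder split (0.50/0.45/0.05 and its mirror image) gives alpha 0.37 with pairwise agreement 0.46. In both, alpha orders the categories opposite to pairwise agreement.

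A second model uses category means 2.5, 5 and 7.5 on the 1–9 scale, residual SD 1.5, and a varying SD between vignettes within a category. Entries are low/moderate/high:

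| Vignette SD | Alpha, 1–9 scale | Alpha, 3 categories | Pairs in same category |
|---|---|---|---|
| 0 | 0.00/0.00/0.00 | 0.00/0.00/0.00 | 0.62/0.52/0.62 |
| 0.25 | 0.02/0.02/0.02 | 0.01/0.02/0.01 | 0.62/0.52/0.62 |
| 0.5 | 0.07/0.08/0.08 | 0.05/0.06/0.05 | 0.63/0.51/0.63 |
| 1.0 | 0.23/0.24/0.24 | 0.16/0.20/0.16 | 0.65/0.50/0.65 |
| 1.5 | 0.38/0.40/0.38 | 0.29/0.35/0.28 | 0.67/0.53/0.67 |

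Alpha follows the vignette SD, while pairwise agreement hardly moves. On three categories, moderate has the highest alpha in every row with SD above 0, and the lowest pairwise agreement in every row.

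**Step 4. An index that works.** Keep De from the pooled set and take Do per vignette. With the Step 2 probabilities and the nominal metric, pooled proportions are 0.37/0.26/0.37, so De = 1 − (0.1369 + 0.0676 + 0.1369) = 0.6586. The index is 1 − 0.1818/0.6586 = 0.72 for low and for high, and 1 − 0.56/0.6586 = 0.15 for moderate. Their mean, 0.53, equals the pooled nominal alpha, 1 − 0.3079/0.6586.

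**The case against.** The strongest reply is that the phrase is loose. The data form an incomplete rater-by-vignette matrix, and the appeal to unbalanced data makes most sense if vignettes are the units of one alpha. That reading is fair, and it yields a usable index of overall agreement. It does not deliver the vignette-level agreement that the sentence gives as its purpose.

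A second reply is that an article may leave the matching of hypotheses to tests to a fuller document. That is right as far as it goes, and the absence of a stated HP3 test would not be a point alone. Here, though, the article does fix the primary agreement index, and under neither reading can that index address HP3. The mixed models do not fill the gap: as described, they model the level of the ratings, not their dispersion.

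Third, alpha is the primary agreement index, not the whole primary analysis; the mixed models are the main analytical approach. A column of exact zeros would also be noticed. Both are true and limit the harm.

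A reader might further infer that alpha within a risk category must be close to zero, or that HP3 will certainly be answered wrongly. The document supports neither. It never specifies a within-category alpha. Near-zero values arise only if vignettes in a category are almost interchangeable. The phrase "using different vignette sets drawn from the same risk-calibrated pool" hints at that, but no within-category spread is given, and with more spread the calculations reach about 0.2 to 0.6.

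**Conclusion.** Wrong as written. The literal rule returns 0, or an undefined value, for every vignette; this is exact and rests on no assumption. The pooled reading is valid for overall agreement by group or condition, but provides neither vignette-level agreement nor the comparison in HP3. Within-category alpha is no substitute, because it reflects the spread between vignettes relative to rater noise. It can be near zero despite high agreement, or rank the categories wrongly, and which of these occurs depends on a spread the document does not state. All figures in Steps 2 to 4 depend on assumed rating distributions and on six vignettes per category, so they illustrate the mechanism and do not forecast results.

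**What to change.** State that Krippendorff's alpha is computed with all 18 vignettes as units, separately by study group and condition, with bootstrap intervals (resampling participants) for the alphas and their differences.

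For vignette-level agreement and HP3, pre-specify one within-vignette index that does not depend on the spread between vignettes, and compare it across risk categories. Two suitable choices are the proportion of rater pairs in the same category, or 1 − Do/De with De fixed from the pooled 18 vignettes; with an ordinal metric, the distances should be fixed from the pooled set too. Either is acceptable; what matters is naming one before ratings are analysed.

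HP3 refers to all study groups. If groups and conditions were equal in size, 500 participants give 500/20 = 25 per cell and 25 × 6/18 ≈ 8 baseline ratings per vignette. Group-specific results should therefore be summarised over the vignettes of a category and shown with intervals.

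The cost is analysis wording and a short script. Design, randomisation and data collection are unchanged.
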